### Participant timeline {13}

Figures 1 and 2

**Fig. 1 Fig1:**
[figure not shown]
Data acquisition across trial timeline

**Fig. 2 Fig2:**
[figure not shown]
Flow diagram of trial timeline

#### Sample size {14}

Sample size calculations for the trial balanced considerations of what size of intervention effect might be considered important or meaningful for our primary outcome (internalising symptoms) in a public health context [13, 39], meta-analytic evidence indicating that SEL interventions typically reduce internalising symptoms by *d* = 0.19–0.24 [17, 19] and, pragmatic factors (i.e., the number of schools that could feasibly be recruited given funding and time constraints).

The following sample size calculations were carried out by the trial statistician in R, following the method outlined in Bloom, Richburg-Hayes and Black [40]. We conservatively power our primary outcome for a minimum detectable effect size (MDES) of 0.19. With alpha = 0.05, power = 0.80, intra-cluster correlation coefficient = 0.04 [41], 20% of outcome variance predicted by child-level covariates (including baseline scores; no variance explained by school-level covariates) [32], and with approximately 40 children per cluster [42] minimum of 52 schools are needed to detect an MDES of 0.16 (as well as to allow for an effective minimisation procedure and variation in underlying empirical parameters), with approximately 26 schools per arm and a total sample of 2080 children. We will oversample by c.15% to mitigate against school-level attrition. Our initial recruitment target is therefore 60 schools, yielding a total sample of 2400 children. However, we will recruit more schools, if possible, in order to maximise statistical power and provide greater protection against attrition.

For the qualitative strand, we are engaging 5 case study schools. In each of these schools, we will engage with the classroom teachers responsible for delivering Passport (*n* = 5) and members of senior leadership (*n* = 5). We will also engage with small groups of 5–6 children in each school, but will over-recruit to account for nonresponse and nonattendance, inviting 8 children to take part in each school, amounting to a possible n of 40 children in total. Using 5 schools allows us to explore a sufficient level of richness and detail of implementation in different contexts given our revisiting to the same schools over time.

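### The sample-size section credits 52 schools with an MDES of 0.16, but its own inputs give 0.19, leaving no margin at that size

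*Protocol article*

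**What the plan says.** All of this is in the protocol article, Sample size {14}. The target comes first: "We conservatively power our primary outcome for a minimum detectable effect size (MDES) of 0.19". The next sentence lists the inputs: "With alpha = 0.05, power = 0.80, intra-cluster correlation coefficient = 0.04", then "20% of outcome variance predicted by child-level covariates" with "no variance explained by school-level covariates", and "approximately 40 children per cluster". From these it concludes that a "minimum of 52 schools are needed to detect an MDES of 0.16", with about 26 schools per arm and 2080 children. A parenthesis gives 52 schools a further purpose: "as well as to allow for an effective minimisation procedure and variation in underlying empirical parameters". The section then adds about 15% more schools, reaching 60 schools and 2400 children, and assigns that increase to the loss of whole schools. Sequence generation {16a} gives 1:1 allocation. The sidedness of alpha is not stated.

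**The concern.** Two different MDES values, 0.19 and 0.16, are attached to one calculation, and every input needed to check them is printed. If 0.16 were right, 52 schools would have real room to spare against the 0.19 target, and the remark about absorbing parameter variation would be fair. If 0.19 is what 52 schools deliver, that room does not exist.

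This matters because 0.19 is the lower end of the meta-analytic range the trial relies on (0.19 to 0.24). A stated sensitivity of 0.16 tells readers that the design reaches comfortably below that range, when it sits at its edge. The margin is also what would protect the trial if the ICC were higher than assumed, or if fewer than 40 children per school were analysed. Pupil loss is a live possibility: under Recruitment {15}, assent is sought again at every wave, and children who do not assent complete no measures.

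**Working it through.** **Inputs.** From Sample size {14}: ICC ρ = 0.04; child-level R² = 0.20; school-level R² = 0; n = 40 per school; alpha 0.05; power 0.80; J = 52 or 60 schools. From Sequence generation {16a}: P = 0.5. I take alpha as two-sided and test the one-sided reading below.

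**Formula** (two-level, school-randomised):

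MDES = M × SE, with SE = √{[ρ + (1 − ρ)(1 − R²)/n] / [P(1 − P)J]}

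M is the sum of the critical value and the power quantile. It is 1.960 + 0.842 = 2.802 with normal quantiles. With t quantiles on J − 2 degrees of freedom it is 2.857 at J = 52 and 2.850 at J = 60.

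**Attempt to reproduce 0.16 at 52 schools**

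- Numerator: 0.04 + 0.96 × 0.80/40 = 0.04 + 0.0192 = 0.0592
- Denominator: 0.25 × 52 = 13
- SE = √(0.0592/13) = 0.0675
- MDES = 2.857 × 0.0675 = **0.193** (normal: 2.802 × 0.0675 = 0.189)

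The printed 0.16 is not reproduced. The 0.19 target is.

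**60 schools**

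- SE = √(0.0592/15) = 0.0628
- MDES = 2.850 × 0.0628 = **0.179** (normal: 0.176)

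**Power, two-sided** (non-central t, normal in brackets)

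| Schools | Power for 0.16 | Power for 0.19 |
|---|---|---|
| 52 | 64% (66%) | 79% (80%) |
| 60 | 71% (72%) | 84% (86%) |
| 74 | 80% (81%) | 91% (92%) |

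In balanced designs, an MDES of 0.16 needs 74 schools (normal) to 76 (t), that is 2960 to 3040 children.

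**Could another reading give 0.16 at 52 schools?** (t version)

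| Reading | MDES at 52 schools |
|---|---|
| One-sided alpha, other inputs as stated | 0.170 |
| 20% of total variance, all at child level | 0.192 |
| 20% removed at both levels, two-sided | 0.179 |
| 80 children per school | 0.176 |
| One-sided and 20% removed at both levels | 0.158 |
| ICC 0.02 | 0.158 |

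Only the last two reach 0.16. The first of them conflicts with "no variance explained by school-level covariates", and the second with "intra-cluster correlation coefficient = 0.04". Cluster size cannot close the gap either. With unlimited pupils per school, the between-school term alone gives 2.857 × √(0.04/13) = 0.159.

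**Is there an allowance at 52 schools?** The values below are my assumptions, chosen to show sensitivity (t version).

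| Departure | MDES, 52 schools | MDES, 60 schools |
|---|---|---|
| None | 0.193 | 0.179 |
| ICC 0.05 | 0.208 | 0.193 |
| 36 analysed per school (10% loss) | 0.196 | 0.182 |
| 32 analysed per school (20% loss) | 0.200 | 0.186 |

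At 52 schools, power for 0.19 is 72% with ICC 0.05 and 76% with 32 analysed per school.

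**Pupil loss in the plan's figures.** 52 × 40 = 2080 and 60 × 40 = 2400, so 40 per school is carried through unchanged. The abstract describes the 2400 as pupils at baseline. The only allowance is 60/52 = 1.154, and the section assigns it to schools.

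**The case against.** The strongest reply is that the design does what it set out to do. The declared target is 0.19. The 52 schools meet it (80% power by the normal calculation, 79% by t), and the 60 to be recruited give 84% to 86%. The number of schools, the primary analysis and the decision rule do not depend on 0.16. That stands, and it is why no change to recruitment is called for.

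It can also be said that there is some slack: 60 schools give 0.179 against 0.19, and the section says more will be recruited if possible. That is true if schools are retained. But the section gives the extra eight schools to school attrition and ties the allowance for parameter variation to the 52, where there is none.

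A third point is that 0.16 may come from an undisclosed input rather than a slip, since sidedness is not given and the hypothesis is directional. One-sided testing at 60 schools does give 0.158. The text, however, ties 0.16 to 52 schools, 26 per arm and 2080 children, where one-sided testing gives 0.170. The printed sentence fails on either reading, though the sidedness should be stated.

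Finally, the source for 40 per school cannot be seen, so the figure might already be net of pupil loss. The abstract's description of 2400 pupils at baseline points the other way. The effect is modest in any case: at 60 schools the MDES stays within 0.19 even with 20% loss.

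What a null result rules out will be set by the confidence interval reported, not by the planning MDES, so I do not rest the point on how a null result might be read.

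**Conclusion.** The concern holds. On the stated inputs with two-sided alpha, 52 schools have an MDES of 0.19 (0.189 to 0.193), not 0.16, and 60 schools have 0.18 (0.176 to 0.179). Power for 0.16 is about 64% to 66% at 52 schools and 71% to 72% at 60, against the 80% claimed; about 75 schools would be needed. The statement that 52 schools leave room for variation in the parameters is unsupported, because at 52 schools the 0.19 target is met with nothing over.

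The error lies in the claimed sensitivity and margin; the trial is still adequately sized for its declared target. The conclusion does not turn on t versus normal quantiles or on sidedness. The figures for ICC 0.05 and for pupil loss rest on my assumed values and only illustrate the lack of margin.

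**What to change.** In Sample size {14}:

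- Replace 0.16 with 0.19 as the MDES for 52 schools, and add 0.18 for 60. If 0.16 came from inputs not reported, the sponsor should disclose them and reconcile them with the printed ones.
- State whether alpha is one- or two-sided.
- Delete the claim that 52 schools allow for variation in the parameters.
- Give the MDES for a smaller analysed cluster as well. With 36 and 32 children per school it is 0.196 and 0.200 at 52 schools, and 0.182 and 0.186 at 60.

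The cost is a few words and figures in one section and a slightly less favourable stated sensitivity. Recruitment, the primary analysis and the decision rule are unaffected.

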### Trial design {8}

A two-arm (intervention vs. control) parallel cluster randomised controlled trial design, incorporating a mixed-methods implementation and process evaluation (IPE), will be used. Schools will be the unit of randomisation. Random allocation will take place following completion of baseline measures (T0), with minimisation ensuring balance across trial arms in school size and the proportion of children eligible for free school meals (FSM). This trial will follow a superiority framework (i.e., we hypothesise that the intervention is superior to usual practice).

Schools allocated to the intervention arm will implement *Passport* to Year 5 classes in the academic year 23/24. Implementing teachers will receive initial training followed by a booster session during the school term. Schools allocated to the control arm will continue to deliver the usual school curriculum. Child-level outcomes will be assessed annually at baseline (T0), post-intervention (T1), and 12-month post-intervention follow-up (T2).

The IPE will include a qualitative strand comprising case studies of 5 purposively sampled intervention schools (to include interviews with teaching staff and members of the senior leadership team alongside pupil focus groups), and a quantitative strand comprising teacher surveys focusing on usual practice in promoting SEL, outcomes (such as stress), and implementation (among those in intervention schools).

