### Recruitment {15}

Recruitment of schools began in October 2022 and will be completed in February 2023. The recruitment strategy follows successful practices established in our previous large-scale school-based projects, namely: relevant contacts in each LA (Local Authority) (e.g., primary education mental health lead) nominating interested schools to participate in the trial, followed by formal invitation from the trial manager. In parallel, we are also leveraging recruitment efforts through mutual stakeholders with strong existing relationships with primary schools in the city region and neighbouring areas, in addition to directly contacting schools, as necessary.

Following successful recruitment at school-level, we will commence recruitment of the trial’s target population: children in Year 4 at baseline (T0). All schools will send information sheets and consent forms to parents/carers of these children prior to T0, providing them the opportunity to opt their child out of the trial. Children will provide assent to participate prior to completion of each annual wave of outcome data collection. Those who do not assent will not complete outcome measures.

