### Plans to promote participant retention and complete follow-up {18b}

To promote retention, all participating schools will receive feedback on outcomes across the trial generally and their school specifically. To guard against differential attrition, schools allocated to the control arm will receive Passport training and materials (if the alternative hypothesis is met) or the financial equivalent (if the null hypothesis is met).

To complete follow-up, the trial manager will send reminder emails and telephone calls (as needed) to teachers of classes with missing teacher or pupil data to maximise the volume of follow-up data collected.

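### The sample-size section allows for school loss but no pupil loss, and on its own inputs 52 schools support an MDES of about 0.19, so the target has almost no margin once the spare schools are gone

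*Protocol article*

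**What the plan says.** Sample size {14} sets the target: "We conservatively power our primary outcome for a minimum detectable effect size (MDES) of 0.19". Its inputs begin "With alpha = 0.05, power = 0.80, intra-cluster correlation coefficient = 0.04". They continue with 20% of outcome variance explained by child-level covariates, none by school-level covariates, and roughly 40 children per school. The section then gives 52 schools (26 per arm, 2080 children) as the minimum, but attaches an MDES of 0.16 to that number.

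On attrition it says "We will oversample by c.15% to mitigate against school-level attrition", followed by "Our initial recruitment target is therefore 60 schools, yielding a total sample of 2400 children". It adds that more schools will be recruited if possible.

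Two other sections bear on pupil loss. Recruitment {15} says: "Children will provide assent to participate prior to completion of each annual wave of outcome data collection"; children who do not assent complete no measures. The retention section {18b} plans reminders to "teachers of classes with missing teacher or pupil data". No expected rate of pupil loss, or of school loss, is given.

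**The concern.** The same figure of 40 serves for the children recruited per school and for the children analysed per school. The calculation therefore treats every recruited pupil in a retained school as giving a primary-endpoint score. The article's own procedures (assent at each wave, chasing of missing pupil data) show that some will not.

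This would matter little if there were slack. The 0.16 beside the 52 schools suggests that there is: a design able to detect 0.16 could lose schools and pupils and still detect 0.19. If 52 schools support only about 0.19, that slack disappears. The stated 80% power for 0.19 then depends on keeping some of the spare schools or losing almost no pupils. A null result would be read against that power figure.

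**Working it through.** **Inputs** (all from Sample size {14} unless noted)
- Alpha 0.05. Sidedness is not stated; two-sided is taken.
- Power 0.80; ICC 0.04; child-level R² 0.20; school-level R² 0.
- n = 40 children per school; J = 52 schools as the minimum, 60 as the target.
- 1:1 allocation (Sequence generation {16a}).
- Pupil loss of 10% and 20%, so n = 36 and 32. This is an assumption.

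**Formula** for a two-level cluster trial with equal arms:

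SE = sqrt(4 x [ICC + (1 - ICC)(1 - 0.20)/n] / J), and MDES = M x SE.

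M is 1.960 + 0.842 = 2.802 by the normal approximation. By t it is t(0.975) + t(0.80) on J - 4 degrees of freedom, because the school level carries an intercept, the arm and two minimisation covariates. For J = 52 that is 2.860. Using J - 2 instead changes the MDES by less than 0.0005.

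**Step 1: the plan's own figure, 52 schools of 40**
- Bracket: 0.04 + 0.96 x 0.80/40 = 0.04 + 0.0192 = 0.0592.
- SE: sqrt(4 x 0.0592/52) = 0.0675.
- MDES: 2.802 x 0.0675 = 0.189 (normal); 2.860 x 0.0675 = 0.193 (t).

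The 0.16 does not reproduce. Solving for J by the normal version gives 4 x 0.0592 x (2.802/0.16)² = 72.6, so 73 schools (75 by t). Solving for 0.19 gives 4 x 0.0592 x (2.802/0.19)² = 51.5, so 52 schools (54 by t). The 52 thus belongs to 0.19. Of the variants tried, only a one-sided test with 20% school-level R² brought 52 schools to 0.16 (0.158), and that contradicts the stated zero school-level R².

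**Step 2: the oversample**
- 52 x 1.15 = 59.8, rounded to 60; 60/52 = 1.154. The c.15% is right.
- The loss it absorbs is 8/60 = 13.3%. A 15% loss from 60 would leave 60 x 0.85 = 51.

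**Step 3: school loss and pupil loss together**

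| Schools | Pupils per school | MDES, normal | MDES, t | Power for 0.19, normal / t |
|---|---|---|---|---|
| 60 | 40 | 0.176 | 0.179 | 86% / 84% |
| 60 | 36 | 0.179 | 0.182 | 84% / 83% |
| 60 | 32 | 0.183 | 0.186 | 83% / 82% |
| 52 | 40 | 0.189 | 0.193 | 80% / 79% |
| 52 | 36 | 0.192 | 0.196 | 79% / 77% |
| 52 | 32 | 0.197 | 0.201 | 77% / 76% |
| 51 | 40 | 0.191 | 0.195 | 80% / 78% |

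Only the bracket changes with n: 0.04 + 0.768/36 = 0.0613, and 0.04 + 0.768/32 = 0.0640. At 52 schools, losing two pupils per school (n = 38, a 5% loss) already takes the normal-approximation MDES to 0.191.

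**The case against.** Much can fairly be said for the plan.

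- **The oversampling sentence is accurate.** A reader might infer that the plan predicts 15% school attrition and then fails to cover it. It does not: it names an oversampling percentage, qualified as approximate, and 60/52 matches it. The gap between 13.3% and 15% is one school.
- **School loss alone does little harm.** A reader might infer that 0.19 is missed in the very situation the oversample is for. That situation is school loss, and at 52 schools 0.19 is met by the normal approximation and is 0.003 away by t. At 51 schools the miss is at most 0.005. The article specifies no degrees of freedom and plans a bootstrap interval, so the t version has no special claim.
- **The clear miss needs an assumed rate.** The article gives no pupil-loss rate. Parents are offered the opt-out before baseline, so those children may never be among the 40, and the source for the 40 is not at hand. Reminders and possible extra recruitment also count in the plan's favour.
- **Unequal school sizes.** One might argue that variation in school size lowers power further, because the design has schools allocated "with minimisation ensuring balance across trial arms in school size". That sentence concerns balance between arms and says nothing about the spread of analysed pupils per school, so no size can be put on this.

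What remains is narrower. Loss between baseline and the primary endpoint cannot already be inside the 40, because the recruited and analysed figures are identical. The possible extra schools have no number attached. The apparent headroom from the 0.16 does not exist.

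**Conclusion.** The point holds as a gap in the stated calculation, of modest size. No pupil-level loss enters the numbers, and the stated inputs put 52 schools of 40 at an MDES of 0.189 to 0.193, so the 0.16 is unsupported and the 0.19 target has almost no margin at the school count the oversample protects. With all eight spare schools lost and 10-20% of pupils lost, the MDES is 0.192-0.197 (normal) or 0.196-0.201 (t), and power for 0.19 is about 76-79% against the stated 80%.

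This rests on a two-sided test, the article's ICC and R² values, equal school sizes and an assumed pupil loss. The documents do not support the conclusion that the trial is seriously underpowered: the shortfall is at most about four percentage points of power, and with all 60 schools retained 0.19 is still met under the same pupil loss.

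**What to change.** In Sample size {14}:

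1. State the number of pupils per school expected in the primary analysis at T1, separately from the number recruited, with the assumed pupil loss behind it. Baseline collection was due to finish in July 2023 (Trial status) and this version is dated September 2023, so observed baseline numbers per school should be available to inform it.
2. Say that 60 schools absorb a school loss of about 13%.
3. Replace the 0.16 and 0.19 with a single MDES that follows from the stated inputs after both losses: about 0.19 to 0.20 if 10-20% of pupils are lost. State the sidedness of the test alongside it.

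No further recruitment is asked for. The cost is a few sentences of text, and the published figure becomes slightly less favourable.

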### Recruitment {15}

Recruitment of schools began in October 2022 and will be completed in February 2023. The recruitment strategy follows successful practices established in our previous large-scale school-based projects, namely: relevant contacts in each LA (Local Authority) (e.g., primary education mental health lead) nominating interested schools to participate in the trial, followed by formal invitation from the trial manager. In parallel, we are also leveraging recruitment efforts through mutual stakeholders with strong existing relationships with primary schools in the city region and neighbouring areas, in addition to directly contacting schools, as necessary.

Following successful recruitment at school-level, we will commence recruitment of the trial’s target population: children in Year 4 at baseline (T0). All schools will send information sheets and consent forms to parents/carers of these children prior to T0, providing them the opportunity to opt their child out of the trial. Children will provide assent to participate prior to completion of each annual wave of outcome data collection. Those who do not assent will not complete outcome measures.

### Recruitment for qualitative IPE strand

We anticipate sampling schools by first requesting expression of interest from intervention schools to maximise the likelihood of engagement with qualitative data generation. To ensure maximum variability in contextual/compositional features (e.g., size, socio-economic status of catchment area) and usual SEL practice based on our baseline survey, 5 schools will be purposively sampled from those who express interest in being a case study site.

Staff (i.e., teachers and members of senior leadership) and children in the 5 purposively sampled intervention schools will be invited to take part in qualitative data generation for our IPE. Information sheets and consent forms will be sent to staff. Children will be invited to take part in focus groups by way of information packs. These will be sent to the schools in advance and given to each child to take home. Parents will be asked to return their consent form to the school and each child’s written assent will be sought prior to the commencement of the focus group. The interviews and focus groups will first take place during implementation of the intervention and at a second time point shortly after intervention delivery is completed.

## Assignment of interventions: allocation

### Sequence generation {16a}

Schools will be allocated 1:1 to either Passport or standard curriculum via minimisation; the allocation sequence will be generated via MinimPy software [43].

